### Covariate Measures

The baseline patient characteristics at the time of the initial visit with the PCP in which inclusion criteria are met will be assessed. Demographic characteristics to be collected will include patient age, sex, race, ethnicity, and insurance. Baseline clinical characteristics to be collected will include clinic blood pressure, number of medications, and comorbidities. Additionally, we will assess the number of clinic visits during the follow-up period.

### Statistical Methods

#### Sample Size

Our sample size estimate is based on the clinical outcome of medication adherence after 12 months, which is measured as a continuous variable. We plan on a 6-month enrollment period. Based on the preliminary data from primary care practices in our health system, we estimate a median of 182 eligible patients per practice during this period. Based on our prior work of having MAs perform counseling related to adherence, we anticipate a group difference of at least 20% between the intervention and the control groups [15]. Applying this effect size to our study, and assuming 80% power, 5% type I error rate (α), 30% attrition over the 18-month study period, and an intraclass correlation coefficient of 0.15 to account for clustering of patients within sites, we estimate a necessary sample size of 10 practices in the study. Calculations of sample size were estimated using a standard approach (eg, design effect) for cluster randomized trials [25].

#### Descriptive Analyses

We will summarize baseline characteristics, clinical outcomes, and quantitative implementation outcomes. Frequencies and percentages will be used to describe categorical variables, and means and SDs will be used to characterize continuous outcomes. Medians and IQRs will be reported for continuous variables that exhibit skewness.

#### Analyses of Primary and Secondary Outcomes

The analysis of all outcomes will follow the intention-to-treat principle. For the intention-to-treat approach, all participants randomly assigned to one of the 2 arms will be included in the analysis under their assigned group, regardless of compliance. The primary study outcome will be PDC, which can take on values ranging from 0% to 100%. We will develop a generalized linear mixed model with PDC as the dependent variable. The model will include a categorical indicator variable for the randomized study arm (control as reference), a variable corresponding to time (baseline as reference), and the interaction of the 2, representing the primary independent variable. The primary study end point will be at 12 months, with secondary end points measured at 6 and 18 months; these secondary end points will be used to assess sustainability. We will also adjust for any sociodemographic or clinical covariates imbalanced at baseline, as well as the number of clinic visits per patient to assess the frequency of exposure to intervention. The model will include practice-level random effects to account for clustering of patients within clinics during randomization. Prior to analyzing the data, we will compare dropout and missing data across the 2 arms and examine whether any patient characteristics were associated with the missing data. If necessary, additional analyses utilizing multiple imputation methods will be conducted.

The secondary study outcome will be blood pressure, also measured as a continuous variable using a similar generalized linear mixed model approach. Exploratory outcomes will include subgroup analyses to identify individual components of the intervention that may be influential on the clinical outcomes and other EHR-based measures.

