### Recruitment and Randomization

This study will use a practice-level cluster randomized design, with 1:1 randomization of 10 practices, resulting in 5 per study arm. We will use block randomization of 4 to 6 practices at a time with go-lives occurring approximately monthly to stagger the intervention rollout across the network.

Recruitment will be performed through email outreach to medical directors and practice managers at individual practice sites. The email will contain a brief description of the project, expectations of the practice for participation, and an offer to have a virtual meeting to present the project and answer additional questions.

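### Adjustment covariates are chosen by observed baseline imbalance with no criterion stated, and the listed model has no term for randomisation block; a short fixed set plus block should replace the rule

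*Protocol article*

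**What the plan says.** In Analyses of Primary and Secondary Outcomes, the primary model is a generalized linear mixed model for PDC with arm, time (baseline as reference) and their interaction, the interaction being the term of interest. "The model will include practice-level random effects to account for clustering of patients within clinics during randomization". On covariates: "We will also adjust for any sociodemographic or clinical covariates imbalanced at baseline". No metric, threshold or level (patient or practice) is attached to that rule. Blood pressure is to be analysed in a similar way.

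The candidates are in Covariate Measures: "Demographic characteristics to be collected will include patient age, sex, race, ethnicity, and insurance", and "Baseline clinical characteristics to be collected will include clinic blood pressure, number of medications, and comorbidities". That makes 5 + 3 = 8 if comorbidities count as one item, and more if they are taken singly.

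The design is in Recruitment and Randomization: a practice-level trial "with 1:1 randomization of 10 practices, resulting in 5 per study arm". On blocking: "We will use block randomization of 4 to 6 practices at a time with go-lives occurring approximately monthly". Block does not appear among the model terms.

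The covariate sentence continues with clinic visits ("as well as the number of clinic visits per patient to assess the frequency of exposure to intervention"). That term is fixed rather than selected, and is a separate matter.

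**The concern.** A covariate helps the analysis when it predicts the outcome. This rule admits covariates for a different reason, an observed difference between arms. A weak predictor that happens to differ gets in; a strong one that happens to balance stays out. The model cannot be written down until the arms have been compared, and because imbalance is not defined, two analysts following the text could fit different models to the same data.

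Cluster allocation makes this worse. Whole practices go to one arm, so patient characteristics differ between arms simply because practices differ. Patients are also identified at visits after their practice was randomised, so differences need not be chance alone.

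The block belongs here too. It is fixed by the design and, because go-lives are staggered, it carries calendar time. It is a natural member of a prespecified adjustment set.

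**Working it through.** The protocol gives no figure of its own for this point. Its sample size of 10 practices is not affected.

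**1. How many covariates would be flagged by chance?**

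Inputs from the protocol: 5 practices per arm; 182 patients per practice (Sample Size: "we estimate a median of 182 eligible patients per practice during this period"); 8 listed covariates. Assumed: the covariate intraclass correlation r. The 0.15 in Sample Size is for the outcome, so r is shown over a range.

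Standardised mean difference (SMD) between arms for a covariate with no true difference:

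Var(SMD) = 2 × [r/5 + (1 − r)/(5 × 182)]

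At r = 0.05 this is 2 × [0.0100 + 0.95/910] = 0.0221, so the SD is 0.149. Then P(absolute SMD > 0.1) = 2 × [1 − Φ(0.1/0.149)] = 0.50, and 8 × 0.50 = 4.0 covariates.

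For an ordinary 5% test that ignores clustering:

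P(flag) = 2 × [1 − Φ(1.96/√(1 + 181r))]

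At r = 0.05 this is 2 × [1 − Φ(1.96/√10.05)] = 0.536, and 8 × 0.536 = 4.3.

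Expected number flagged out of 8:

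| Assumed r | SMD above 0.1 | Unclustered 5% test | SMD above 0.2 | Cluster-aware 5% test |
|---|---|---|---|---|
| 0 | 0.3 | 0.4 | 0.0 | 0.4 |
| 0.01 | 1.6 | 1.9 | 0.1 | 0.4 |
| 0.02 | 2.6 | 2.9 | 0.4 | 0.4 |
| 0.05 | 4.0 | 4.3 | 1.4 | 0.4 |
| 0.10 | 5.0 | 5.2 | 2.6 | 0.4 |
| 0.15 | 5.5 | 5.7 | 3.4 | 0.4 |

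The last column is 8 × 0.05. The chance of at least one flag there is 1 − 0.95^8 = 0.34, taking the covariates as independent. At the same r, the adjustment set can be nearly empty or more than half the list, depending on a criterion the text does not give.

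**2. Does the selection distort the test?**

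A null simulation (2,000 runs per setting, r from 0.02 to 0.10, t-test on covariate-adjusted practice means) gave type I error of 0.03 to 0.05 with imbalance-selected covariates and 0.04 to 0.06 with fixed ones. The SD of the estimate was 0.247 to 0.272 outcome SD when selected and 0.246 to 0.256 when fixed. There is no inflation, and at most a modest loss of precision.

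**3. Does the selection move the planned estimate?**

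With an identity link and complete data, the main effect of a time-constant covariate cancels from arm-by-time, so the shift is zero. With 30% attrition, two simulations gave a mean shift of about 0.01 outcome SD and a maximum between 0.02 and 0.05.

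**4. Block.**

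Ten practices in blocks of 4 to 6 make two blocks (taken as 4 + 6). Practice-level degrees of freedom go from 10 − 2 = 8 to 7, and the critical t from 2.306 to 2.365, a ratio of 1.026.

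A block main effect moved arm-by-time by zero with complete data and by at most 0.0003 SD with attrition, so a main effect alone does nothing in this model. In a simulation where waves were made to differ over time, the true SD of the estimate was 0.24; the mean model standard error was 0.28 without block and 0.23 with it. The 95% half-widths are 2.306 × 0.28 = 0.65 and 2.365 × 0.23 = 0.54. The size depends on the assumed wave differences, for which the protocol gives no figure.

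**The case against.** The strongest reply is that the primary term is an interaction with time. The listed covariates are baseline characteristics, so under an identity link the choice among them hardly touches the primary estimate. This stands and removes most of the practical weight for continuous PDC and systolic pressure. It does not cover everything: the article does not name the link, and cancellation is only approximate under another one. For the binary outcome of PDC at or above 80%, every included patient is below the threshold at baseline by eligibility, so there is no baseline variation against which covariates could cancel.

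A second reply is that thresholds, lists and block terms are usually left to the analysis plan, which is not shown. That is fair for the missing threshold taken alone, and if the analysis plan already includes block, that part is met. But the covariate rule is stated in the article, and defining imbalance more precisely would not make it a good reason to adjust.

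A reader might go further than the documents allow in four ways:

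- **Inflated type I error.** The simulation did not show it.
- **A long list using up the 8 practice-level degrees of freedom.** The listed covariates are patient-level, with about 10 × 182 = 1,820 patients. Only practice-level terms such as block draw on the 8.
- **Many covariates will certainly be flagged.** This is conditional on a patient-level criterion and on assumed correlations. A cluster-aware test flags few.
- **Baseline PDC is ignored.** It is already in the model as the response at the reference time.

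Nor does the article say who judges imbalance, or when.

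**Conclusion.** The point holds in a limited form. The rule makes the adjustment set for the primary and secondary models depend on the data and on an unstated criterion. Between about 0.4 and about 3 to 5 of the 8 listed covariates would enter by chance, the upper range resting on patient-level criteria (SMD above 0.1 or an unclustered 5% test) and assumed covariate correlations of 0.02 to 0.10. The listed model also omits block, which can make the standard error too large if waves differ over time.

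The harm is an unfixed model and some lost precision. It is not a demonstrated bias or error-rate failure: under an identity link the shift in the arm-by-time estimate is small. The change is worthwhile mainly because it is cheap. The article expects primary outcomes to be assessed in fall 2024, after its publication, so prespecification was still possible when it appeared.

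**What to change.** Replace the imbalance clause with a short set fixed before any outcome data are seen, drawn from Covariate Measures (for example age, sex, insurance and number of medications), and use it in all outcome models.

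Add randomisation block so that it acts on the 12-month contrast: block-by-time in the repeated-measures model, or block as a main effect in a model of the 12-month outcome alone.

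Do not add baseline PDC or baseline blood pressure as a covariate while it is also a response at the baseline time point. Keep it as the baseline response, or use it as a covariate only if baseline is removed from the response.

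Report baseline differences descriptively, and keep adjustment for imbalanced covariates as a sensitivity analysis with its criterion stated.

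Cost: one paragraph and about one practice-level degree of freedom (8 to 7; critical t 2.31 to 2.36). No change to data collection or to the number of practices.

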### Intervention

The intervention is an EHR-based workflow that consists of four components: (1) identification of patients with poorly controlled hypertension and low medication adherence at the point of care; (2) prompts for the MA to screen for important barriers to medication nonadherence; (3) alerting the PCP of low medication adherence and important barriers, with the intent of facilitating a conversation with the patient regarding medication adherence; (4) clinical decision support (CDS) to assist PCPs in addressing the barriers to medication adherence. These components have been informed through interviews and usability sessions with PCPs and MAs as well as a patient survey [19]. The process for intervention begins when the MA records the blood pressure of a given patient presenting to see their PCP. If the blood pressure is recorded as ≥140/90 mm Hg, the algorithm within the EHR will automatically screen the patient for the other inclusion criteria. If the patient meets all the criteria, that is, if their age is ≥18 years, the prior blood pressure is ≥140/90 mm Hg, they are taking an antihypertensive medication, and their PDC <80%, the MA will then receive a CDS alert to ask the patient about whether 1 of the 6 barriers contributed to missing medications (Figure 1). These 6 barriers are based on a validated questionnaire and survey of the patient population in our health system [19-21]. After responding to the question, the MA will receive an alert to communicate this result to the PCP, either through secure chat or through another method (Figure 2). The PCP then will receive the secure chat message, which will include a prompt to review the CDS related to medication adherence (Figure 3). Even if the message is not communicated from the MA to the PCP, the passive CDS will still be available to the PCP. The CDS will convey the barrier to medication adherence and provide suggestions to address the barrier (Figure 4). Additionally, the CDS will link to an order set, which will include auto documentation related to medication adherence and barriers, appropriate patient instructions, and an International Classification of Diseases, Tenth Revision (ICD-10) diagnostic code to add to the visit (Figure 5). Ultimately, our goal is for these tools to facilitate a discussion between the PCP and the patient to address barriers to medication adherence.

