### Clinical Outcomes

Clinical outcomes will be based on the data extracted from the EHR. Our primary outcome will be medication adherence assessed at 12 months. Adherence will be measured by PDC as a continuous variable using a lookback period of 6 months. The secondary clinical outcomes will be medication adherence as measured as a binary variable of PDC ≥80% [1,2] and clinic systolic blood pressure assessed continuously. When available, we will use the mean of the last 2 clinic blood pressure measurements within 1 year of the initial clinic visit, in order to increase reliability with multiple blood pressure measurements [22].

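### The outcome models adjust for clinic visits made during follow-up, a post-randomisation measure of exposure, so the arm-by-time contrast may not be the intention-to-treat effect

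*Protocol article*

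**What the plan says.** All quotes are from the protocol article.

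- Analyses of Primary and Secondary Outcomes sets the principle: "The analysis of all outcomes will follow the intention-to-treat principle". It names the model, "We will develop a generalized linear mixed model with PDC as the dependent variable", with terms for arm, time (baseline as reference) "and the interaction of the 2, representing the primary independent variable".
- The same paragraph then adjusts this model for covariates found imbalanced at baseline, "as well as the number of clinic visits per patient to assess the frequency of exposure to intervention". It describes no primary model without visits and does not label the visit adjustment as sensitivity or exploratory. Blood pressure is to be analysed with a similar model.
- Covariate Measures lists the baseline characteristics and then adds: "Additionally, we will assess the number of clinic visits during the follow-up period". This is the only visit count that the article defines.
- Intervention ties delivery to visits: "The process for intervention begins when the MA records the blood pressure of a given patient presenting to see their PCP".
- Clinical Outcomes fixes the endpoint: "Our primary outcome will be medication adherence assessed at 12 months".

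**The concern.** The visit count is complete only after the practice has been randomised and the index visit has passed. The intervention acts at visits: it flags low adherence, screens for barriers and prompts the primary care provider to discuss them. That could make patients return more often or less often. If it does, visits lie on the path from arm to PDC, and adjusting for them removes part of the effect the trial is meant to estimate.

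Visits can also share unmeasured causes with pharmacy fills, such as engagement or severity of illness. If the arm also shifts visits, conditioning on them links arm to those causes and can produce an arm difference where none exists.

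The article itself describes the covariate as exposure to the intervention. An effect adjusted for exposure received answers a different question from the one an intention-to-treat analysis answers. At stake is the meaning of the primary estimate in a trial of 10 practices.

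**Working it through.** **Inputs from the article.** The contrast is arm by time at 12 months. There are 10 practices, 5 per arm, with a median of 182 eligible patients each and 30% attrition: 182 × 0.7 = 127.4 per practice. For the effect size, "we anticipate a group difference of at least 20% between the intervention and the control groups", read here as 20 PDC points. The article gives no visit frequency, no effect of arm on visits, no SD of PDC and no link function, so there is no figure of its own to reproduce. Everything below about visits is assumed.

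**Step 1. One fixed total per patient, main effect only, linear model, complete data.** For patient i with arm A, visit total V and time T (0 or 1):

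Y = a + b1·A + b2·T + b3·A·T + g·V

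The change from baseline is Y(1) − Y(0) = b2 + b3·A. V cancels, so b3 is unaffected whatever the arm does to visits.

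**Step 2. Visits that accumulate from zero at baseline.** The change is now b2 + b3·A + g·V, so V no longer cancels. The adjusted b3 differs from the total effect by about −D × g, where D is the arm difference in mean visits and g is the within-arm slope of PDC on visits. A comparison of 12-month values only, adjusted for visits, behaves the same way.

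The table assumes a true arm effect of zero, with the slope due only to an unmeasured patient factor. Simulations used n = 400,000 without clustering.

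| D (visits) | g (points per visit) | −D × g | Simulated, 12-month only | Simulated, arm × time, cumulative visits |
|---|---|---|---|---|
| 0.5 | 3 | −1.5 | −1.51 | −1.4 |
| 0.5 | 5 | −2.5 | −2.53 | not run |
| 1 | 3 | −3.0 | −2.83 | −3.0 |
| 1 | 5 | −5.0 | −4.91 | −5.0 |

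Against 20 points this is 1.5/20 = 7.5% to 5/20 = 25%. The sign reverses if D or g is negative, for example if sicker patients visit more and fill less.

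**Step 3. The same forms with a true effect of 20 points.** Simulated with 10 practices of 127 patients, complete data and no between-practice variance, fitted by least squares. Assumptions: about 3 visits by 12 months in the control arm, 2 PDC points gained per visit, and a patient factor that raises both visits and PDC (6 points per SD). The last column comes from a companion simulation under the same assumptions.

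| Extra visits in the intervention arm | Arm × time, no visits | + fixed total | + cumulative visits | 12-month only, + visits |
|---|---|---|---|---|
| 0 | 19.9 | 19.9 | 19.9 | 20.0 |
| 0.5 | 19.9 | 19.9 | 18.1 | 18.3 |
| 1 | 20.2 | 20.2 | 16.8 | 16.6 |
| 2 | 20.3 | 20.3 | 13.6 | 13.1 |

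With 1 extra visit, no effect of visits on PDC and only the shared patient factor, the 12-month estimate moves from 20.0 to 18.6. That loss comes entirely from conditioning on visits.

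**Step 4. Link function.** On a logit scale with 1 extra visit, the contrast moves from 0.816 to 0.828 with a fixed total and to 0.689 with cumulative visits. With no extra visits it moves from 0.808 to 0.816 and 0.823.

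**Step 5. Does the term measure exposure?** A visits term common to both arms includes control visits, which carry no exposure to the intervention. Within the intervention arm, the alert fires only when blood pressure and PDC still meet the criteria, so a visit is not necessarily an exposure. The form that leaves the contrast intact therefore does not do what the term was added to do.

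**The case against.** The strongest reply is that the plainest reading of the plan is the harmless one. A per-patient count suggests one total, no interaction of visits with time or arm is stated, and Step 1 shows that such a term cannot move the arm-by-time contrast in a linear model with complete data. This stands. The 1.5 to 5 points must not be read as the bias of the model the article specifies; they belong to forms it neither adopts nor excludes.

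Second, no described component of the intervention schedules a return visit, and the article nowhere says that visit frequency will change. This also stands: the path from arm to visits is plausible but assumed.

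Third, a reader might infer that the plan breaches its own intention-to-treat rule. The article defines that rule as analysing participants in their assigned group whatever their compliance, and a covariate neither excludes nor moves anyone. The difficulty lies in what the adjusted coefficient estimates, not in who is analysed.

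Fourth, visits might help with missing data. With about 30% of 12-month values missing in a way that depended on visits (an assumption), a linear run with a true effect of zero, 1 extra visit and a slope of 5 gave a bias of −0.48 points without the term and 0.02 with it. The gain is small and does not require visits in the effect model: the article already foresees multiple imputation, where visits could serve as an auxiliary variable.

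These replies limit the size and certainty of the problem. They do not supply a reason to keep the term. The adjustment is a stated rule, not a detail left open.

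**Conclusion.** The point holds in a conditional form. The plan adjusts its primary model, and by extension the blood pressure model, for a post-randomisation variable that the intervention could affect. The adjusted contrast may therefore not be the randomised effect.

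- **Zero bias:** a fixed per-patient total as a main effect in a linear model with complete data; or, on the linear scale, any of the forms examined if the arm does not change visits.
- **About 1.5 to 5 PDC points, either sign:** visits accumulated over time or a 12-month-only comparison, given an arm difference of 0.5 to 1 visit and a slope of 3 to 5 points per visit. Both ranges are assumptions.
- **Under a logit link:** a small shift for a fixed total and a clear one for cumulative visits when the arm changes visits.

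It is tempting to conclude that the primary estimate is certainly no longer the randomised effect. The article does not support that, because it fixes neither the form of the visits term nor the link, and does not say that visits will differ by arm. None of the forms examined both guarantees the randomised contrast and measures exposure as intended. The planned 10 practices do not depend on this covariate.

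**What to change.** Delete the visit adjustment from the primary PDC model and from the secondary outcome models. Report follow-up visits by arm as a descriptive process measure. If frequency of exposure is of interest, put it in a separately labelled exploratory dose or mediation analysis. If a utilisation covariate is wanted, use visits before the index visit.

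The cost is one sentence in the protocol or analysis plan. The follow-up count is still used, the sample size is unchanged and no patient is affected; a pre-index visit count would be one more field to extract from the health record. The change should be made before outcome data are compared by arm.
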